### Patient Inclusion

Potential participants will be identified and recruited during hospitalizations in one of the participating sites. An EPR-embedded clinical rule identifies in near-real time all hospitalized patients with a BLAL in the allergy module. After checking inclusion and exclusion criteria, all eligible patients will be included in this study.

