### Baseline Measurements

For each patient, baseline data will be recorded in the electronic case report form using the REDCap (cf. Infra). The collected information will encompass sociodemographic details, clinical data, and specific information on the BLALs as registered in the EPR. Sociodemographic information will include age, gender, and contact details of both the general physician and the community pharmacist. Clinical information will capture the reason for admission and, if applicable, the condition requiring antibiotic treatment, categorized according to the *ICD* (*International Classification of Diseases*) codes. Additionally, any antibiotics (Anatomical Therapeutic Chemical codes J) already administered during the current hospitalization will be documented. To assess comorbidity burden, the presence of specific conditions contributing to the Charlson Comorbidity Index will be recorded, including myocardial infarction, congestive heart failure, peripheral vascular disease, cerebrovascular disease, dementia, chronic pulmonary disease, rheumatologic disease, peptic ulcer disease, liver disease, diabetes, hemiplegia or paraplegia, renal disease, malignancy (localized or metastatic), leukemia, lymphoma, and acquired immunodeficiency syndrome. Information on BLALs will be extracted from the allergy registration module within the EPR. This will include the registration date of the BLAL, the specific drug involved (Anatomical Therapeutic Chemical code), the onset date of the allergic reaction, reported symptoms, and the source of information. Additionally, the probability of label accuracy, as indicated by the reporter, will be documented.

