### AFC CDS Tool (Intervention Group)

A clinical rule embedded in the EPR checks in near-time for re-exposure to the culprit antibiotic or class member, from the date of BLAL registration to the date of patient inclusion (the AFC). The AFC is incorporated into the hospital information system as an “if-then” algorithm, using real-time structured data available in the EPR. The AFC incorporates information from the electronic prescribing module in the EPR and uses an integrated natural language processing tool to identify re-exposures since the introduction of the BLAL in the various EPR records. Additionally, it lists data on coadministration of antihistamines, glucocorticoids, or epinephrine during the re-exposure period, up to 24 hours after the last antibiotic dose. These medications are considered proxies for possible allergic reactions and help inform the subsequent review process. The results of the screening, that is, the clinical rule alerts, are compiled on a structured worklist in the hospital information system for secondary review by a specified trained person, that is, a member of the study team in the current study, before alerting the treating physician [24]. Validated flowcharts are used to support the review, ensuring a standardized and systematic approach. Schematic algorithms are used to guide the actual delabeling or refinement advice based on the allergy label, subsequent exposure, and consequences linked to this exposure (Figure S3 in Multimedia Appendix 1).

Consulting primary care data could not yet be automated due to the lack of interoperability between different EPRs. In order to retain a focus on the impact of the AFC alone, we did not systematically obtain information from the primary care HCP (physician and/or pharmacist) on beta-lactam re-exposure. In our pilot study [30], this step provided only a minor contribution.

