Based on the collected information, BLALs are allocated to 3 groups: to delabel, to refine, or to leave as such. An incorrect BLAL is assigned when patients reported a clearly nonallergic adverse drug reaction, when a negative rechallenge or uneventful re-exposure was identified since registration of the BLAL; a correct BLAL is assigned when an allergic reaction was observed in the hospital or when positive skin and/or provocation testing was found; and an undetermined BLAL is assigned when there is no proof of correctness or incorrectness of the BLAL. Allocation is performed by a member of this study’s team, and if needed, discussed and validated with the principal investigator.

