### BLAL Adjustment (Intervention Group, if Applicable)

In the case of a correct or undetermined BLAL, no action will be taken. In case of an incorrect BLAL, a suggestion will be sent to the treating physicians in the EPR (“follow-up note”), to delabel (re-exposure to the culprit found) or to refine (harmless exposure to nonculprit beta-lactams, excluding monobactams or carbapenems found) the BLAL accordingly. The note will include a summary of the algorithm’s findings, a suggestion for review of the label in consultation with the patient, a reference to the in-house delabeling procedure (written and video), and contact details for questions and additional information. If the BLAL is not changed in the following 24‐72 hours, the treating physician will be contacted by phone to discuss potential delabeling; reasons to discard the advice will be noted in the electronic case report form (as part of the process evaluation) and in the formal study report (cf. Infra). A distinction is made between definite tolerated re-exposure and presumed tolerance. The former is scored in case of documented administration through the electronic prescribing module (in which prescription and registered administration are required), in the EPR, and/or when bedside uneventful re-exposure could be orally confirmed by the treating hospital physician. The latter is scored when free-text notes or ambulatory prescriptions of antibiotic delivery are identified in the EPR, in the absence of EPR-registered bedside verification by the treating hospital physician.

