### Sample Size Determination

The main aim of our study is to establish the assumed superiority of using the AFC over SOC in increasing the proportion of patients with first-line antibiotics prescribed. Therefore, we look at the proportion of patients receiving first-line or narrow-spectrum beta-lactam antibiotics within the total number of patients receiving antibiotics. The crossover design accounts for seasonal as well as intra- and interhospital differences in overall antibiotic use. Nevertheless, overall antibiotic use will be monitored at the participating sites during this trial’s period.

The following assumptions were applied.

For the control arm, in a recent retrospective study in UZ Leuven, involving 21,999 patients with pneumonia, pyelonephritis, infections associated with heart, kidney, liver, or lung transplantation; appendectomy; coronary artery bypass grafting; and total knee or hip replacement, we investigated the difference in antibiotic use between patients with and without BLAL [21]. It showed that 10.5% of patients with a BLAL received amoxicillin despite their label. Based on the latter, we estimate that 10% of the patients in the control group already receive first-line antibiotics. We add a 5% increase due to indirect learning of our protocol because we cannot exclude that treating physicians learn to use discordances in the medical file for delabeling or refinement of the allergy labels, independent of our study and AFC tool. Considering around 30% of hospitalized patients receive antibiotics during their stay [34], this brings the percentage down to 4.6% in the control group.

For the intervention arm, we previously showed that our CDS approach has the potential to delabel 38% of BLALs [30]. We add a margin of 5% for physicians or patients who refuse to delabel or be delabeled [9]. Considering around 30% of hospitalized patients will receive antibiotics during their stay, this results in an overall estimate for the intervention group of 9.9%.

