### Statistical Analysis

The primary endpoint is cumulative guideline-concordant use of first-line and/or narrow-spectrum beta-lactam antibiotics according to IGGI-based local guidelines, assessed across predefined assessment windows up to day 100 (days 1, 30, and 100). Within each window, guideline concordance is scored at the patient level in an any or ever manner as 1 if at least one in-hospital systemic antibiotic course is guideline-concordant and 0 if otherwise. If multiple courses occur within a window, the window is considered concordant if any course meets guideline criteria. This any or ever approach was chosen in line with the quality-improvement objective of the AFC intervention, capturing whether appropriate first-line therapy was achieved within a care window while limiting instability due to multiple within-episode treatment changes. Windows without in-hospital systemic antibiotic administration are considered not applicable (“no opportunity”) and are excluded from the denominator.

For each patient, a cumulative weighted guideline-concordance score is calculated at day 100 as the proportion of applicable windows with guideline-concordant therapy (*sᵢ/nᵢ*). The primary comparison between intervention (AFC) and control will use a binomial generalized linear mixed-effects model with logit link, modeling *sᵢ* out of *nᵢ*, including fixed effects for study phase and period, and a random intercept for hospital to account for clustering in the crossover design. A prespecified adjusted model will additionally include age, sex, and the Charlson comorbidity index. Patients without any applicable windows will be excluded from this analysis and reported separately. The primary estimand targets the period during which the AFC is expected to plausibly influence prescribing through contemporaneous decision support and short-term label adjustment.

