Secondary endpoints include guideline-concordant beta-lactam use at each individual assessment window (including day 200), delabeling or refinement rate, beta-lactam tolerance, antibiotic switching, ICU admission, readmission, resistant organism outcomes, LOS, mortality, and cost outcomes. Outcomes at day 200 are analyzed as secondary durability measures, as longer-term prescribing may be influenced by label reappearance or documentation changes unrelated to the index intervention. Secondary endpoints will be analyzed using hierarchical mixed-effects models appropriate to outcome type (binary, continuous, or time-to-event), with fixed effects for study phase and period and clustering by hospital. Process evaluation outcomes will be analyzed descriptively.

Predefined subgroup analyses will assess potential effect modification by including phase-by-subgroup interaction terms in the primary model. Subgroups of interest are BLAL type (penicillin vs other labels), reported reaction severity category, time since label registration, infection type (prophylaxis vs therapeutic indication), ICU admission status, and hospital type (academic vs regional). Subgroup analyses will focus on the primary endpoint and are considered exploratory and hypothesis-generating. 

Moreover, because the AFC is expected to influence prescribing primarily through label delabeling or refinement, we will perform an exploratory implementation analysis within the AFC phase. Patients will be classified as with implementation if the BLAL was delabeled or refined after the AFC recommendation, and as not with implementation if otherwise. The cumulative primary endpoint (*sᵢ/nᵢ* up to day 100) will be summarized by implementation status; any between-group comparisons will be considered descriptive and interpreted cautiously, as implementation is a postallocation process measure and may be confounded.

No formal adjustment for multiplicity will be applied. Secondary and subgroup analyses will be interpreted with caution.

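### In the exploratory implementation analysis, a beta-lactam course already running at inclusion can both prompt the label change and be scored as a success

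*Protocol article*

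**What the plan says.** The article builds the chain across several Methods subsections.

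- **Patient Inclusion:** patients are found during the stay: "An EPR-embedded clinical rule identifies in near-real time all hospitalized patients with a BLAL in the allergy module".
- **Baseline Measurements:** treatment before inclusion is expected, since any antibiotics "already administered during the current hospitalization will be documented".
- **AFC CDS Tool:** the search covers "re-exposure to the culprit antibiotic or class member, from the date of BLAL registration to the date of patient inclusion". It stops at inclusion, not at admission, and no exception is stated for the index stay. A label counts as incorrect when, among other grounds, an "uneventful re-exposure was identified since registration of the BLAL".
- **BLAL Adjustment:** an incorrect label leads to advice "to delabel (re-exposure to the culprit found) or to refine", the latter after harmless exposure to another beta-lactam.
- **Statistical Analysis, endpoint:** each window (days 1, 30 and 100) is "scored at the patient level in an any or ever manner as 1 if at least one in-hospital systemic antibiotic course is guideline-concordant".
- **Statistical Analysis, implementation analysis:** "Patients will be classified as with implementation if the BLAL was delabeled or refined after the AFC recommendation"; all other AFC-phase patients form the comparison group. The same score up to day 100 is summarised in both. The text calls this exploratory and descriptive and warns that implementation arises after allocation and may be confounded.

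**The concern.** The implementation analysis is there because the AFC is expected to act mainly through label change. That reading needs the label change to come before the prescription it is credited with.

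For some patients the order can be reversed. A first-line beta-lactam is started despite the label, is still running at inclusion, is picked up as the re-exposure, and leads to the label change. The same course makes an early window concordant. The outcome event then helps to decide which group the patient is in.

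This is not confounding in the usual sense, where a third factor drives both variables. Adjusting for age, sex and comorbidity would not remove it; recorded dates would. What is at stake is the interpretation of a descriptive analysis: a tool that changed no prescription could still appear to work through label change.

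**Working it through.** The plan states no figure for this contrast, so there is none to reproduce. The check asks what the analysis would show if the label change had no effect on prescribing.

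**Inputs**
- *b*, concordance among treated patients: 15%, from the 10% control estimate plus 5% for learning in Sample Size Determination. As a check on that reading, 15% × 30% treated = 4.5%, close to the stated 4.6% (10.5% in place of 10% gives 4.65%).
- *h*, flagged on exposure before the index stay, taken as independent of *b*: 10% (the proof-of-concept study in the Introduction, penicillin labels only) or 38% (the planning figure, from a protocol that also used clinical history and primary care contact).
- *u*, share of flags implemented: 33/38 = 87%, from the plan's 38% less its 5% refusal margin. This is a planning value, not an observed acceptance rate.
- *r*, share of concordant patients whose course was running at inclusion and itself raised the flag: not in the document, so varied. The article does report that "10.5% of patients with a BLAL received amoxicillin despite their label", which makes overlap plausible but does not measure it.

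**Formulas** (one binary window)
- P(flag and concordant) = b[r + (1 − r)h]
- P(flag) = b[r + (1 − r)h] + (1 − b)h
- Concordance with implementation = P(flag and concordant) / P(flag); *u* cancels
- Concordance without = [b − u·P(flag and concordant)] / [1 − u·P(flag)]

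**Worked case**, h = 0.10, r = 0.20:
- P(flag and concordant) = 0.15 × (0.20 + 0.80 × 0.10) = 0.042
- P(flag) = 0.042 + 0.85 × 0.10 = 0.127
- With implementation: 0.042 / 0.127 = 33.1%
- Without: (0.15 − 0.0365) / (1 − 0.1103) = 12.8%

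| h | r | With | Without | Gap (points) |
|---|---|---|---|---|
| 0.10 | 0 | 15.0% | 15.0% | 0 |
| 0.10 | 0.1 | 25.1% | 13.9% | 11 |
| 0.10 | 0.2 | 33.1% | 12.8% | 20 |
| 0.10 | 0.5 | 49.3% | 9.2% | 40 |
| 0.38 | 0.2 | 19.0% | 12.9% | 6 |
| 0.38 | 0.5 | 24.3% | 9.5% | 15 |

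Over a wider grid (b 10% or 15%, r 25% to 100%, h 10% or 38%, u 50% or 95%) the smallest gap is 13.5% versus 9.1%, about 4 points (b = 10%, r = 25%, h = 38%, u = 50%). The largest is 63.8% versus 1.0%, about 63 points (b = 15%, r = 100%, h = 10%, u = 95%).

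**A limit of the model.** It lets only concordant running courses raise a flag. A non-concordant beta-lactam running at inclusion could also do so, and would pull the other way. If a share *q* of non-concordant patients is flagged like this, (1 − b)h becomes (1 − b)[q + (1 − q)h]. With h = 0.10, r = 0.20 and q = 0.10 this term is 0.85 × 0.19 = 0.1615, and the result is 0.042 / 0.2035 = 20.6% versus (0.15 − 0.0365) / (1 − 0.1767) = 13.8%. With q = r the gap vanishes. A *q* below *r* is plausible, because a concordant course is by definition a beta-lactam, whereas antibiotics from other classes cannot raise the flag.

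**After the fix.** If courses running at inclusion are left out of both s_i and n_i, the flag carries no information about the remaining courses in this model, and the gap is 0.

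**The case against.** The strongest reply is that the article already limits this analysis. It is exploratory, the comparison is descriptive, caution is promised, and no test or conclusion rests on it. That stands and sets the severity. It does not dispose of the point, because the warning names confounding and a reader would not infer from it that the scored course may be the one that prompted the label change.

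Second, the day-1 anchor and the handling of running courses may be in Table S1 or in the analysis plan still to be finalised. That is possible. But anchoring the window at inclusion would not by itself exclude a course still running then, and the look-back and scoring rules given in the article permit the overlap.

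Third, a flag is not a label change. A study team member reviews alerts with flowcharts and algorithms that are not shown, and reaction-proxy drugs are listed up to 24 hours after the last dose, which suggests that some running courses may not yet be judged uneventful. This stands: the text permits the sequence but does not show how often it occurs.

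Fourth, the actual score spans up to three windows, so later windows may dilute a single-window artefact. This also stands; the figures above illustrate scale and do not forecast the trial's result.

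A reader might also infer that the beta-lactam tolerance endpoint counts the triggering exposure. The article does not say which exposures enter that endpoint, so the inference has no support.

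**Conclusion.** The point holds in a limited form and is minor. As written, the same course can place a patient in the implemented group and supply that patient's success, and the stated caveat does not cover this. The spurious gap runs from a few points to several tens of points, given no AFC effect, one binary window, an assumed share of index-stay triggers, and few or no flags raised by non-concordant running courses. The true share is unknown.

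Two stronger readings are tempting and fail. One is that the whole implementation analysis is circular. It is not: re-exposures before the index admission, and labels judged incorrect because the reaction was clearly non-allergic, are unaffected. The other is that the primary result is biased in favour of the AFC. Courses already running at inclusion count in both phases, so they dilute that contrast rather than create it.

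**What to change.** Change the implementation summary only, in the analysis plan before database lock:

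1. Use one time origin for both groups and score only courses started after the date of inclusion. Because the look-back ends on that date, this removes every possible trigger. Treat windows with no such course as not applicable, in line with the existing rule for windows without antibiotics.
2. For each flagged patient, derive from the recorded dates whether the triggering re-exposure came before the index admission or within it. Show patients flagged on index-stay exposure separately.
3. Keep the planned s_i/n_i summary beside this one if wanted, with a sentence stating the overlap.

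Starting the clock at the recommendation for flagged patients and at inclusion for the rest would also remove the triggers, but it gives the groups unequal follow-up, so a common origin is better.

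The cost is one derived variable and fewer scored windows in an exploratory summary. A course begun between inclusion and the label change would still be scored, and the existing caution about confounding still applies. The primary endpoint and its model stay as they are.

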### BLAL Adjustment (Intervention Group, if Applicable)

In the case of a correct or undetermined BLAL, no action will be taken. In case of an incorrect BLAL, a suggestion will be sent to the treating physicians in the EPR (“follow-up note”), to delabel (re-exposure to the culprit found) or to refine (harmless exposure to nonculprit beta-lactams, excluding monobactams or carbapenems found) the BLAL accordingly. The note will include a summary of the algorithm’s findings, a suggestion for review of the label in consultation with the patient, a reference to the in-house delabeling procedure (written and video), and contact details for questions and additional information. If the BLAL is not changed in the following 24‐72 hours, the treating physician will be contacted by phone to discuss potential delabeling; reasons to discard the advice will be noted in the electronic case report form (as part of the process evaluation) and in the formal study report (cf. Infra). A distinction is made between definite tolerated re-exposure and presumed tolerance. The former is scored in case of documented administration through the electronic prescribing module (in which prescription and registered administration are required), in the EPR, and/or when bedside uneventful re-exposure could be orally confirmed by the treating hospital physician. The latter is scored when free-text notes or ambulatory prescriptions of antibiotic delivery are identified in the EPR, in the absence of EPR-registered bedside verification by the treating hospital physician.

### Communication of the AFC Results (Intervention Group, if Applicable)

In case of an incorrect BLAL, this study’s member will make a formal report of the AFC result in the EPR (Figure S4 in Multimedia Appendix 1), available for hospital physicians and, after validation of the coordinating investigator, also for the patient in the Mynexuzhealth app. This report is also sent to the primary care HCP via e-letter through the eHealth platform. The report will include a summary of our findings and, if applicable, label adjustment. Patients are referred to their primary care HCP, this study’s information letter for participants, and this study’s webpage with contact details of this study’s team for further questions and/or disagreement with the label adjustment.

